#### Mechanistic outcome measures

The trial will evaluate the possible mechanisms underlying any changes in the primary and secondary endpoints. The effect of ondansetron on whole gut transit will be measured at baseline and 12 weeks (*n* = 400), using radio-opaque markers and an abdominal x-ray as previously described [27]. High-resolution manometry will be performed at baseline and after 8–11 weeks of treatment at two centres (*n* = 40) to assess whether ondansetron decreases the number of high-amplitude propagating contractions and increases the percentage time occupied by cyclical retrograde propagated contractions [11]. Barostat assessment will be performed at baseline and after 8–11 weeks of treatment at four centres (*n* = 80, some of whom may also undergo manometry), in order to assess if ondansetron increases rectal compliance and decreases sensitivity (manifested as increased pressure thresholds for pain and urgency). Serum will be sampled to genotype patients for polymorphisms in the *TPH1* gene (*n* = 400), and correlation tested between these and the mucosal 5HT and TPH-1 mRNA obtained from high-rectal biopsies (*n* = 80), final ondansetron dose, and responder status, to see whether this predicts sensitivity and/or response to ondansetron. Finally, stool sample analysis (*n* = 400) will be used to assess whether ondansetron reduces total faecal bile acid and tryptase concentrations, and correlation will be tested between these and any changes in urgency.

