### Trial design

TRITON is a multi-site, parallel group, randomised, double-blind, placebo-controlled trial with embedded mechanistic studies within selected sites. Our aim is to determine the superiority of ondansetron compared with placebo. In total, 400 patients with IBS-D will be randomised 1:1 to receive either ondansetron or placebo. Both treatments will be administered in oral doses of between 4 mg every third day and 24 mg daily for 12 weeks. Dose titration will be undertaken in the first 2 weeks of the trial to avoid constipation, which at a standard dose occurs in one quarter of patients. The primary outcome will be assessed over the 12 weeks post randomisation. Secondary and safety outcomes will be measured up to 16 weeks following randomisation. See Fig. 1 for an overview of the trial procedures. The Standard Protocol Items: Recommendations for Interventional Trials (SPIRIT) checklist is provided as an Additional file 1.

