## Methods

### Trial setting

This trial will be performed initially at 18 sites in the UK. All sites will be required to recruit patients, perform all necessary protocol assessments, and offer patients the opportunity to take part in the whole-gut transit assessment and the blood and stool collection. In addition, four of the sites will perform the mechanistic assessments for the trial. Patients at all sites will be offered an opportunity to take part in the mechanistic studies but will be required to travel to one of the specified sites for these assessments.

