The patient will return 2 weeks later to confirm eligibility. The diary will confirm they have had stool consistency BSFS 6–7 for more than 2 days a week and do not have only BSFS 7 for 7 days per week, and a weekly average worst pain score ≥ 30. Patients who consent to the whole gut transit study will be dispensed Transit-Pellet capsules containing markers, and the abdominal x-ray appointment will be confirmed for the morning of visit 3. Patients will take the Transit-Pellet capsules for 6 days prior to visit 3. Patients who have consented to one or both mechanistic studies will have appointments arranged for baseline assessment prior to visit 3.

#### Visit 3

On visit 3, patients will undergo a pregnancy test if applicable, whole gut transit assessment by abdominal x-ray (if they have consented), rigid sigmoidoscopy (if they have consented), completion of baseline questionnaire booklet (including IBS-SSS, SF-LDQ, HADS, PHQ-12, and IBS-QOL questionnaires), and collection of stool, whole blood, and serum samples (if they have consented). Patients will then be randomised and given a 6-week patient diary and the trial medication in accordance with their blinded randomisation allocation. Patients will be asked to record the following on a daily basis: stool frequency, consistency of each stool, worst abdominal pain experienced that day, worst bowel movement urgency, number of trial medication capsules taken, and whether they have used loperamide that day. Every week the diary will ask whether they feel that they have had satisfactory relief from their IBS symptoms that week. If they agree, the patient will continue to receive two text messages each day for the next 6 weeks, asking if they have passed a stool of a consistency of 6 or 7 that day, and what their worst abdominal pain was that day.

During the first 2 weeks patients will be contacted every 2 days by the local site team to discuss bowel habit. The dose of ondansetron or placebo will then be titrated as required. Additional guidance on dose titration will be given to each trial site in a standard operating procedure, and to the patient in a dose titration instruction leaflet. A check for serious adverse events (SAEs) will be performed during each telephone call. The steady dose to be taken forward for the remainder of the trial will be confirmed in week 2, although this may be altered during the 12 weeks if required, to avoid constipation.

#### Visit 4

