### Sample size

TRITON plans to recruit 400 patients from up to 24 sites across England and Scotland. This will provide 90% power at 5% significance to detect a 15% absolute difference between the randomised groups in the proportion of patients achieving the FDA-recommended [28] endpoint of a weekly response for pain intensity and stool consistency for at least 6 weeks of the 12-week treatment period. This difference (15%) is considered to represent the minimum clinically important difference. We have assumed a placebo response rate of 17%, as recently reported using this endpoint and allowed for a 15% attrition rate.

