#### Whole gut transit

Our previous study using the same radio-opaque marker technique as we propose to use showed ondansetron increased whole gut transit time by a mean (95% CI) of 10 (6–14) h. Using 200 patients per group gives 90% power to detect a change of 0.7 h. The larger numbers will also give us the power to test correlation with other endpoints.

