### Data analysis

#### General considerations

All hypothesis tests will be two-sided with a 5% significance level. Methods to handle missing data are described for each analysis. Analysis and reporting will be in line with Consolidated Standards of Reporting Trials (CONSORT) [30]. As TRITON is a double-blind trial, the trial statistician will be blinded to treatment group allocation throughout the trial, until the database has been locked and downloaded for final analysis. Only the safety statistician, supervising trial statistician, back-up safety statistician, and authorised unblinded individuals at the CTRU will have access to unblinded treatment group allocation prior to final analysis.

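### The whole gut transit power counts every randomised patient (200 per group), with no allowance for the planned 15% attrition or for patients who decline the test

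*Protocol article*

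**What the plan says.** All citations are to the protocol article.

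- **Trial design** sets the total: "400 patients with IBS-D will be randomised 1:1", that is, 200 per group.
- **Sample size** says that this total "allowed for a 15% attrition rate".
- **Mechanistic outcome measures** states: "The effect of ondansetron on whole gut transit will be measured at baseline and 12 weeks (*n* = 400"). The same n is given there for stool analysis and genotyping, and again in Mechanistic outcome methods.
- **Whole gut transit** (under Sample size) states: "Using 200 patients per group gives 90% power", for a change of 0.7 h.
- **Trial setting** requires sites to "offer patients the opportunity to take part in the whole-gut transit assessment and the blood and stool collection".
- **Participant timeline**, visit 3, lists "whole gut transit assessment by abdominal x-ray (if they have consented"). The visit 5 text likewise limits the x-ray and the stool and serum samples to consenting patients.
- **High-resolution left-sided colonic manometry** needs 17 patients and aims for 20 on each treatment, explicitly to cover dropouts.
- **Mechanistic studies** compares the groups on change in transit time, so each analysed patient needs both measurements.

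**The concern.** A power statement depends on the patients who contribute data to the comparison. The transit statement uses 200 per group, which leaves no room for a patient who declines the markers and x-ray or who leaves before visit 5. The same article expects both: it makes the test voluntary, and it sizes the trial for 15% loss. The manometry text a few lines later does add a dropout allowance, so the omission for transit is inconsistent within the sizing section.

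At stake is one stated power figure. It also bears on the accompanying remark that the larger numbers will support correlations with other endpoints, since those too depend on how many patients have data at both times.

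**Working it through.** **Inputs.** Two-sided 5% level (General considerations: "All hypothesis tests will be two-sided with a 5% significance level"); 400 randomised 1:1 (Trial design); 15% attrition (Sample size); 200 per group, 90% power and 0.7 h (Whole gut transit). The consent rate is not given, so a range is assumed.

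**Step 1: is 400 already inflated for attrition?** Sample size says "We have assumed a placebo response rate of 17"% and a 15-point difference, so 17% versus 32%. With the usual two-proportion formula (pooled variance under the null, no continuity correction), 90% power needs 171 per group, 342 in total. Then 342 / 0.85 = 402.4, or 403 when rounded up, against 400 stated. (With a continuity correction the result is 368 / 0.85 = 433, which does not match.) So 400 includes the attrition allowance, and the design expects about 400 × 0.85 = 340 completers, 170 per group.

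**Step 2: what the transit statement assumes.** The detectable difference is (1.960 + 1.2816) × SD × √(2/n) = 3.2415 × SD × √(2/n), with n per group. At n = 200 and 0.7 h the implied SD is 0.7 / (3.2415 × 0.1) = 2.16 h. The 90% is reached only with 200 analysable patients per group.

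**Step 3: effect of a smaller n.** For any SD, the detectable difference grows by √(200/n), and power at the original difference is Φ(3.2415 × √(n/200) − 1.96), where n = 200 × 0.85 × consent rate.

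| Consent (assumed) | Pairs in total | Per group | Detectable difference, multiple of stated | Power at stated difference |
|---|---|---|---|---|
| 100% | 340 | 170 | 1.08 | 84.8% |
| 90% | 306 | 153 | 1.14 | 80.9% |
| 70% | 238 | 119 | 1.30 | 70.6% |
| 50% | 170 | 85 | 1.53 | 56.1% |

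At full consent the stated 0.7 h becomes 0.76 h.

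**Step 4: practical weight.** The Whole gut transit text quotes a previous effect of 10 h (95% CI 6 to 14), so SE = 4/1.96 = 2.04 h. The number of patients behind that interval is not given. If it were all 120 recruited to the pilot cross-over, the SD of within-patient differences would be 2.04 × √120 = 22.4 h; with 60 it would be 15.8 h. Taking the larger value as the SD for the group comparison, power for a 10 h effect is 99.4% at 200 per group, 98.5% at 170, 93.2% at 119 and 83.0% at 85.

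These SDs are far from the 2.16 h that the 0.7 h implies. That is a separate difficulty with the 0.7 h figure. It does not alter the ratios in the table, but it is why any restatement needs a stated SD.

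**The case against.** The strongest reply is that n = 400 is a number entered or offered, not a number analysed. The text on outcomes says only that transit will be measured and samples taken. The n = 40 for manometry in the same section is plainly a figure before dropout, since 17 per arm are needed and 20 are recruited. This stands. A reader might infer that the article promises 400 analysed patients for transit, stool and genotype and cannot deliver them, but the documents do not support that:

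- No section calls 400 an analysed number, and optional consent alone does not rule out full uptake.
- Genotype needs one sample at visit 3, taken before randomisation, so later attrition removes none; only consent can.
- No power is stated for stool or genotype, so none is overstated there.

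The reply does not rescue the transit power sentence, because power is a statement about patients with data.

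A second reply is that the 15% is stated for the diary-based primary endpoint, and that applying it to a visit 5 x-ray is an assumption. That is fair, and 340 is a planning expectation, not a ceiling. The assumption is reasonable, because a patient who has left the trial has no visit 5 x-ray. The manometry allowance is also consistent with it (20 × 0.85 = 17).

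A third reply is that little depends on this: an effect as large as the earlier 10 h keeps ample power. This also stands, under the SD assumed in the working, and it keeps the point minor.

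**Conclusion.** The point holds for the transit power statement. It uses the full randomised sample, which already contains the attrition allowance, for a paired and optional measurement. If 15% attrition carries over and every patient consents, the expected size is about 170 per group, the detectable difference is 1.08 times the stated one, and power at the stated difference is about 85%, not 90%. Any non-consent lowers this further; the rates of 90%, 70% and 50% are assumptions, as the article gives none.

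The n = 400 for transit and stool in the outcome sections is an unlabelled denominator, not an arithmetic error. Genotype is not affected by attrition. Severity is minor: one secondary power figure changes and no primary result depends on it.

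**What to change.** - **Whole gut transit:** replace 200 per group by the expected number with paired data, about 170 per group times the expected consent rate. State that rate and the SD used, and restate the detectable difference or the power at that n.
- **Mechanistic outcome measures and Mechanistic outcome methods:** label n = 400 for transit and stool as the number of patients to be offered the measure. Give the expected number with paired data separately (about 340 before non-consent), as a planning figure.
- **Genotype:** describe the sample as consenting patients at visit 3.

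The cost is wording only, with a less favourable stated precision for transit. No extra enrolment is needed.

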### 5HT_3_ receptor antagonist sensitivity

We have also shown that individuals vary widely in their responsiveness to ondansetron, explaining why trials using fixed doses of 5HT_3_RAs result in severe constipation in some patients. When patients were allowed to have dose titration we found that constipation was rare, occurring in only 2% of patients. However, the required dose of ondansetron ranged from 4 mg on alternate days to 8 mg three times a day (t.d.s.). The reasons for this variation are unclear but recent evidence suggests that responsiveness to 5HT_3_RAs might be linked to polymorphisms in the genes controlling 5HT synthesis. Serotonin availability in the rectal mucosa is thought to be determined by the activity of the rate-limiting synthetic enzyme tryptophan hydroxylase-1 (TPH-1), which produces serotonin in enterochromaffin cells. A recent small study showed that TPH-1 mRNA levels in rectal mucosa (and thus presumably serotonin synthesis rate) were approximately doubled in responders to another 5HT_3_RA, ramosetron, compared with non-responders, and that this was linked to the TPH-1 genotype [17]. TPH-1 rs211105 minor allele G was found in 44% of non-responders, but only in 4% of responders, indicating that possessing the major allele increases responsiveness to the drug. It was also associated with worse diarrhoea, possibly because of the greater 5HT synthesis.

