### Intervention

Eligible patients will be randomised in equal proportions to receive either over-coated capsules of ondansetron 4 mg or over-coated placebo, for 12 weeks. The dose of the IMP will be individually titrated during the first 2 weeks by calls from the research team on alternate days, aiming for a stool consistency type 3–5 on the BSFS.

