#### Dose titration

Since the optimum dose varies widely from 4 mg on alternate days up to 8 mg t.d.s., we will start all patients on 4 mg daily and after 2 days contact them to adjust the dose, thus avoiding the complication of constipation. If stool consistency remains loose, patients will be asked to increase their dose in 4-mg steps every 2 days up to the maximum of 8 mg t.d.s. If stools become hard or there is no bowel movement on day 2, they will be asked to stop the drug for 1 day and recommence at a lower dose changing from 4 mg daily to 4 mg on alternate days. If stools still remain hard or infrequent, patients will be asked to reduce their dosage to 4 mg every third day. Patients will discontinue the trial in the unlikely event that their stool remains hard even at this low dose.

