#### Mechanistic studies

Mechanistic studies will be analysed blinded to the intervention allocation, by the site research fellow under supervision of the Chief investigator and local supervising PIs. The differences between treatment groups in changes in whole gut transit times, colonic motility measures (percent time of cyclical retrograde contractions and high-amplitude propagating contraction (HAPC) frequency), rectal compliance, and thresholds for urgency and pain measured using the barostat, faecal bile acid concentrations, and faecal tryptase will each be assessed by linear regression models. In addition, exploratory mediator analyses will explore whether treatment effects, in terms of changes in urgency or pain, are mediated through changes in faecal bile acids or protease. Exploratory subgroup analysis (tests of interactions) will be performed to investigate the effect of the presence of each specified single nucleotide polymorphism allele on response to treatment, using logistic regression with addition of an interaction term for the allele and treatment.

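### The TPH1 test against final ondansetron dose needs adjustment for baseline stool severity before it can be read as a test of drug sensitivity

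*Protocol article*

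**What the plan says.** All references are to the protocol article.

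- **The test.** Mechanistic outcome measures plans to genotype patients for TPH1 polymorphisms and to test correlation with several variables, among them "final ondansetron dose, and responder status, to see whether this predicts sensitivity and/or response to ondansetron". No comparator arm or covariate is named for the dose part.
- **What sets the dose.** Under Intervention, the dose is titrated individually, "aiming for a stool consistency type 3–5 on the BSFS". Under Dose titration: "If stool consistency remains loose, patients will be asked to increase their dose in 4-mg steps every 2 days". Hard or absent stools lead to a reduction.
- **What the genotype is said to do.** The section on 5HT3 receptor antagonist sensitivity describes a small study of ramosetron, "indicating that possessing the major allele increases responsiveness to the drug". The next sentence adds: "It was also associated with worse diarrhoea, possibly because of the greater 5HT synthesis".
- **Placebo.** The Visit 3 text under Participant timeline applies the same procedure to both arms: "The dose of ondansetron or placebo will then be titrated as required". Trial design gives both the same range: "Both treatments will be administered in oral doses of between 4 mg every third day and 24 mg daily for 12 weeks".
- **Genotype and response.** Mechanistic studies, under Data analysis, examines response to treatment "using logistic regression with addition of an interaction term for the allele and treatment". It gives no model for dose.

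**The concern.** A final dose reached by titrating to a stool-form target has at least two causes: how loose the stools would have been without the drug, and how much each step of drug firms them. Only the second is drug sensitivity.

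This matters here because the article ties the genotype to both causes. On the natural reading of the two background sentences, the major allele makes patients more responsive (lower dose needed) and also gives them worse diarrhoea (higher dose needed). The two paths oppose each other. A genotype that affects severity alone would produce a correlation with dose that looks like a sensitivity effect. A genotype that affects both could give a correlation near zero, or one of the wrong sign.

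Understanding how genetic variation in serotonin synthesis bears on responsiveness is part of the stated Objectives, so a misread result would bear on something the trial sets out to learn.

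**Working it through.** **1. The plan's own figure.** The article gives no size or power for the genotype-dose test. Its only related figure is N = 400 for the primary endpoint, which reproduces. With 17% against 32%, two-sided 5% and 90% power, the pooled formula is

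n = [1.960·√(2·0.245·0.755) + 1.282·√(0.17·0.83 + 0.32·0.68)]² / 0.15² ≈ 171 per arm,

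so 342 in total, and 342/0.85 ≈ 403. After 15% attrition, 200 × 0.85 = 170 per arm remain. A final ondansetron dose exists only in the active arm, so about 170 to 200 patients inform this test, not the 400 genotyped.

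**2. The dependence, from the text alone.** Looser stools raise the dose; firmer stools lower it. Genotype is linked to looseness and to drug effect. Dose therefore carries both paths, and a two-variable correlation cannot separate them.

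**3. Illustrative simulation.** None of the genotype inputs is in the documents; all are assumptions.

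- Eight dose levels, expressed as average daily mg: 4/3, 2, 4, 8, 12, 16, 20, 24. Start at 4 mg; seven contacts; 170 per arm; 1,000 trials per setting.
- Stool score at a contact = 5.3 + severity − (ondansetron only) sensitivity × 0.42·log2(1 + dose) + noise (SD 0.8). One step up if above 5.5, one step down if below 2.5.
- Severity has SD 0.6. Log sensitivity has SD 0.4. Minor-allele carriers are 20% or 40% of patients.
- Carriers are milder by 0, 0.3 or 0.6 points (0.3/0.6 = 0.5 SD; 0.6/0.6 = 1 SD). Their sensitivity is either unchanged or multiplied by exp(−0.3) ≈ 0.74.
- Baseline is measured with error SD 0.2, so its reliability is 0.36/(0.36 + 0.04) = 0.90.

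Three tests at two-sided 5%: (a) Spearman correlation in the ondansetron arm; (b) regression in that arm adjusted for baseline; (c) genotype-by-arm interaction in both arms, adjusted for baseline and baseline-by-arm. The table gives the percentage significant, for 20% / 40% carriers.

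| Carriers milder by | Sensitivity differs | (a) plain | (b) adjusted | (c) interaction | Mean Spearman correlation in (a) |
|---|---|---|---|---|---|
| 0 | no | 6 / 6 | 6 / 5 | 6 / 6 | 0.00 / 0.00 |
| 0.3 | no | 40 / 59 | 6 / 6 | 6 / 7 | −0.13 / −0.17 |
| 0.6 | no | 92 / 99 | 7 / 7 | 6 / 8 | −0.25 / −0.31 |
| 0 | yes | 35 / 50 | 59 / 78 | 30 / 44 | 0.12 / 0.16 |
| 0.3 | yes | 5 / 5 | 49 / 65 | 30 / 39 | −0.01 / −0.02 |
| 0.6 | yes | 52 / 67 | 37 / 48 | 32 / 44 | −0.15 / −0.18 |

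Rows 2 and 3 show severity passing as sensitivity. Row 5 shows a real effect cancelled. Row 6 shows it reversed in sign.

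**4. Other assumed settings** (170 per arm, 25% to 40% carriers).

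- Severity effect only, 0.3 to 0.5 SD: the plain correlation is significant in 20–51%, 29–74% or 33–77% of trials, depending on the model.
- Severity effect only, 0.1 SD: 6–8% or 9–10%.
- Opposing effects: power of the plain correlation is 6–24% or 7–13%.
- Baseline adjustment in the ondansetron arm: 5–7% false positives and 67–88% power under opposing effects. With no severity effect it raises power from 64–75% to 85–94%. With a noisier baseline, one model left 6–17% false positives at shifts of 0.2 to 0.5 SD.
- Two-arm interaction: 44–58% or 51–63% power under opposing effects.

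**5. Placebo at the ceiling.** From 4 mg to 24 mg is (24 − 4)/4 = 5 steps; at 2 days each that is 10 days, inside the 2-week titration. Placebo patients whose stools stay loose can therefore reach the maximum capsule level, which leaves the interaction less information.

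**The case against.** The strongest reply has four parts.

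**The text is an outcomes paragraph in a condensed article.** Covariates for an exploratory correlation usually sit in the analysis plan, which is not shown, and Endpoint analysis has a general clause on adjusting regressions for baseline values where applicable. This stands in part: the clause does not exclude adjustment here. But it concerns regression models and is not tied to this correlation, and the text does pair a specific test with a specific interpretation.

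**The dose association has a legitimate use of its own.** The background says the individual dose needed cannot currently be predicted. If genotype predicts the dose reached, through whatever path, that is a true finding. This stands. The unadjusted correlation is wrong only as evidence of sensitivity.

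**The rates are products of assumption.** This stands too. The genotype evidence comes from one small study of another drug, and at a 0.1 SD severity effect the distortion is slight.

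**The placebo arm is not essential.** In these simulations the one-arm adjusted model controls error about as well as the interaction when baseline is well measured, and has more power. A reader might infer that a two-arm ordinal interaction is required; the working does not show that.

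A reader might also count as errors the shared value at the maximum dose and the uncertain final dose of a patient who leaves with hard stools at the lowest regimen. These are details the article leaves open and that a fuller document may settle; nothing in the text is contradicted.

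**Conclusion.** The point holds in a limited form. As written, the genotype-dose correlation cannot by itself support a claim about drug sensitivity, because the dose is driven by stool form and the article links the genotype to stool severity as well as to responsiveness. If the severity effect is material, the test can mislead in either direction.

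The size for this trial is unknown. Across the assumed settings, false indications of sensitivity run from 6–10% at a 0.1 SD severity effect to 20–77% at 0.3 to 0.5 SD. These show direction and possible scale and are not estimates. They depend on the assumed carrier share, effect sizes, titration model and quality of the baseline measure.

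It would be tempting to conclude that the trial's whole genetic analysis ignores the placebo arm. The documents do not support that: the response question already uses an allele-by-treatment interaction across both arms. The primary analysis and N = 400 are untouched, and no dosing rule is questioned.

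**What to change.** 1. Replace the plain correlation with a regression of final titrated dose level on TPH1 genotype in the ondansetron arm, adjusted for baseline stool severity. Name the covariate in advance: loose-stool days per week or mean BSFS from the two-week diary completed before Visit 2.
2. As a supporting check, model the titrated capsule level in both arms with genotype, arm and their interaction, adjusted for baseline severity and its interaction with arm. State that it has less power and that many placebo patients may sit at the maximum capsule level.
3. If an unadjusted correlation is reported, describe it as showing whether genotype predicts the dose reached, not as evidence of sensitivity.

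**Cost.** Analysis wording only. The baseline diary, the daily capsule record and the genotype samples are planned in both arms. In the settings with no severity effect, baseline adjustment raised power, so little is lost if the concern proves empty. Some confounding can remain if the diary measures severity imprecisely, and the report should say so.
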